#### Analyses

Quantitative data will be analysed using the principle of intention-to-treat. Mean differences in EBP competency, as determined by the Berlin tool, between intervention and control groups will be explored using a Student’s t-test. Differences between intervention/control groups and student type (undergraduate/graduate/international) will be explored using one and two-way ANOVA’s, where appropriate.

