**Methods/design:**

This study is mixed methods in design. A randomised controlled trial will examine the effectiveness of blended learning versus didactic approach of teaching EBP to medical students. The primary outcome of the RCT is EBP competency as assessed by the Berlin tool. Focus groups will be conducted to explore student perceptions and attitudes towards implementing a blended learning approach in teaching EBP. A concurrent triangulation design will be implemented, permitting quantitative data to inform the effectiveness of the intervention and qualitative data to contextualise the results.

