### Recruitment

Third year medical students are randomly placed in small tutorial groups for their EBP teaching (approximately 20–25 in a group). Tutorial groups will be randomised to receive EBP teaching adopting a blended learning approach, or the traditional didactic small group learning approach. Students not wishing to participate in the study will be taught via the traditional didactic approach and not be asked to complete an outcome assessment.

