### Randomisation

Participants will be randomised according to their tutorial group (i.e. cluster) by a researcher independent to the study utilising a simple cluster randomisation procedure (computerised random numbers). All students will have access to the blended learning materials at the end of the study period to ensure parity between groups.

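### Whole tutorial groups are randomised, but the primary Berlin score is compared with an ordinary t-test that ignores the groups

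*Protocol article*

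**What the plan says.** - **Unit of randomisation.** Under Recruitment: "Tutorial groups will be randomised to receive EBP teaching adopting a blended learning approach" or the didactic one, with "approximately 20–25 in a group". Under Randomisation: "Participants will be randomised according to their tutorial group (i.e. cluster"), by a "simple cluster randomisation procedure (computerised random numbers"). No stratification by site or student type is stated.
- **How groups arise.** "Third year medical students are randomly placed in small tutorial groups for their EBP teaching" (Recruitment).
- **Primary outcome.** "The primary outcome of the RCT is EBP competency as assessed by the Berlin tool" (abstract, Methods/design).
- **Primary analysis.** Mean differences in the Berlin score "between intervention and control groups will be explored using a Student’s t-test" (Analyses). Comparisons involving student type "will be explored using one and two-way ANOVA’s, where appropriate".
- **Sample size.** At least 120 students per arm, 40 from each of three regions that are also three student types, with a standard deviation of 2.8 (Sample size calculation).

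The article mentions no ICC, design effect, random effect, cluster-robust variance or analysis of group means.

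**The concern.** Student's t-test assumes independent observations. Here a whole group receives one teaching method, and its members then go through ten two-hour sessions together, with small-group work and, in the blended arm, presentations to one another. Random placement into groups limits the correlation that students bring with them. It does not remove the correlation that a shared course creates. Groups may also differ by site and student type.

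With positive correlation, the variance of the difference between arms is larger than the t-test supposes. The p-value is then too small and the 95% interval under-covers. This is the trial's one primary comparison, so blended learning could be declared better, or worse, because a few tutorial groups happened to do well or badly.

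This is not a detail left to an analysis plan. The protocol names a method, and a later plan could correct it only by departing from it.

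**Working it through.** **The plan's own figure.** The 50% difference has no baseline score, so 120 per arm can be neither reproduced nor refuted. Reading β = 0.80 as 80% power, two-sided 5%, SD 2.8, 120 independent students per arm would detect

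2.8 × √(2/120) × (1.960 + 0.842) = 1.01 points.

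The finding does not depend on this figure.

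**Inputs.** Group size m = 20 to 25 (Recruitment) and 120 per arm (Sample size calculation). The ICC is not given, so 0.01 to 0.10 is an assumption.

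**Number of randomised units (derived, at the minimum size and with full groups).** 240/20 = 12 and 240/25 = 9.6, so about 10 to 12 groups. The student-level test uses 240 − 2 = 238 degrees of freedom; a test on group means has 10 − 2 = 8 to 12 − 2 = 10.

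**Formulas.**
- Design effect: DE = 1 + (m − 1) × ICC
- Correct standard error ÷ naive standard error: √DE
- True type I error of the naive test: 2 × [1 − Φ(1.96/√DE)]

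Example, m = 20 and ICC = 0.05: DE = 1 + 19 × 0.05 = 1.95; √DE = 1.396; 1.96/1.396 = 1.404; type I error = 16.0%. The effective sample is 120/1.95 = 61.5 per arm.

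| ICC (assumed) | DE, m = 20 / 25 | SE ratio, m = 20 / 25 | True type I error, m = 20 / 25 |
|---|---|---|---|
| 0.01 | 1.19 / 1.24 | 1.09 / 1.11 | 7.2% / 7.8% |
| 0.02 | 1.38 / 1.48 | 1.17 / 1.22 | 9.5% / 10.7% |
| 0.05 | 1.95 / 2.20 | 1.40 / 1.48 | 16.0% / 18.6% |
| 0.10 | 2.90 / 3.40 | 1.70 / 1.84 | 25.0% / 28.8% |

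**Simulation check.** 40,000 trials per setting with no true difference; 6 groups of 20 or 5 groups of 24 per arm.

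| ICC | Student-level t-test, type I error | Coverage of its 95% interval | t-test on group means, type I error |
|---|---|---|---|
| 0 | 5.0% / 5.0% | 95.0% / 95.0% | 5.1% / 5.0% |
| 0.01 | 7.1% / 7.8% | 92.9% / 92.2% | 5.0% / 4.9% |
| 0.02 | 9.3% / 10.6% | 90.7% / 89.4% | 5.0% / 5.0% |
| 0.05 | 15.7% / 18.0% | 84.3% / 82.0% | 4.9% / 4.9% |
| 0.10 | 25.2% / 28.6% | 74.8% / 71.4% | 4.9% / 5.1% |

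The simulation agrees with the formula. Recruiting more groups of the same size does not help, because DE depends on group size and not on the number of groups.

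**The case against.** **The unit of the t-test is not stated.** A t-test on group means would be valid, and the Analyses section does not say students are the unit. That is true, but nothing points to group means, while the sample size in students and the ANOVAs by student type point the other way. If group means were intended, the text has to say so.

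**The cluster numbers are derived.** Students may decline and go unassessed, so analysed groups may be smaller than 20. This stands as a limit on size. With 15 or 10 analysed students per group, type I error at an ICC of 0.05 is about 13% or 10%. Both are still well above 5%.

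**Regional differences could make the test conservative.** This is the strongest objection. If each arm really has 40 students per region, variation between regions cancels from the difference between arms but stays in the residual. With two groups of 20 per region per arm and a total ICC of 0.05, type I error is about 16% if all the clustering lies within regions, 10–11% if half lies between them, and just under 5% if all does. But the benefit needs exact balance, and simple randomisation does not enforce it. With the 12 groups allocated without restriction, the last two figures become about 15% and 12–13%.

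**Tutor assignment is not described.** A tutor who teaches several groups, perhaps in both arms, would change the correlation structure. This stands: the ICC cannot be known from the document. It is a reason to model the groups and estimate the ICC, not to assume that it is zero.

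**Conclusion.** The concern holds. The stated test does not match the stated design, and the p-value and interval for the primary comparison will be too optimistic if outcomes within tutorial groups are positively correlated, which shared teaching makes likely. For groups of 20 to 25, the nominal 5% error becomes 7–8% at an ICC of 0.01 and 16–19% at 0.05, where coverage falls to about 82–84%.

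The direction rests on a positive ICC; at exactly zero there is no inflation. The size rests on the assumed ICC, on full-sized groups, and on how much of the clustering lies within regions. The t-test in effect assumes an ICC of zero without saying so, and even 0.01 takes the error above the stated level. Because this affects the validity of the primary result, it must be corrected before analysis.

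**What to change.** Replace the t-test in the Analyses section with one of these, named in advance as primary:

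1. a comparison of tutorial-group mean Berlin scores, weighted for group size, using a t distribution with degrees of freedom equal to the number of groups minus the number of fitted parameters; or
2. a linear mixed model on student scores with a random tutorial-group effect and Kenward-Roger or Satterthwaite degrees of freedom.

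Report the estimated ICC. Do not rely on uncorrected GEE or sandwich standard errors with about 12 groups.

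Two refinements are worth making in the same edit. Adjust for student type, since groups come from three student types and randomisation is not stated to be stratified. Apply the same group-level approach to the ANOVAs: 40 students per arm per region is only about two groups per arm, so those comparisons should be presented as exploratory.

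**Cost.** Group membership is known from allocation, so no new data are needed and the edit itself is short. The interval will be wider, and the power shortfall that the t-test hides becomes visible. With six groups of 20 per arm and a true difference of 1.01 points, the standard error is 2.8 × √(2 × 1.19/120) = 0.394 at an ICC of 0.01 and 2.8 × √(2 × 1.95/120) = 0.505 at 0.05. On 10 degrees of freedom that gives power of about 64% and 44%, not 80%. The sample size calculation therefore needs to be revisited alongside this change, although correcting the test does not have to wait for it.

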### Settings and participants

A multi-campus study will be conducted with medical students currently enrolled in the MBBS course at Monash University. Monash University runs undergraduate and graduate-entry MBBS programs, in both Australia and Malaysia. Students are assigned to one of seven metropolitan hospitals, or six rural, hospitals in Australia (with one site in Malaysia). Participants for this study will be third year medical students, who are entering their first year of clinically-based training and first year of formal EBP training.

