### Analyses

#### Sample size calculation

A minimum of 120 students per arm (40 from each of metropolitan Melbourne (undergraduate), rural Victoria (graduate) and Monash Malaysia (international)), will be recruited to detect a 50% difference in EBP competency (α = 0.05, β = 0.80, σ = 2.8) between groups.

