## Discussion

It has been more than 20 years since the term 'evidence based practice’ first emerged, yet there is currently little evidence to guide educators on how to teach EBP to health professionals. This study will provide novel RCT evidence regarding the effectiveness of blended learning as a methodological approach for teaching EBP in medical schools. It will also provide evidence on the effectiveness of blended learning across medical student cohorts; be it undergraduate, graduate and international students. It will also provide valuable qualitative data to contextualise results, particularly student perception of competency in EBP.

## Appendix 1

Interview schedule used to guide focus group discussions

1. What type of material do you prefer to be taught in; (and why)

••Lecture format

••Tutorial format

••Small groups

••Self-directed

••Online

••Workshops

2. How is EBM best delivered (probe reasoning for responses)

••Lecture

••Tutorial

••Online

••Combination etc…

3. Would 'flip’ learning suit the teaching of EBM (i.e. pre-loading information before class)? (probe reasoning for responses)

4. Should EBM teaching be blended with;

••Bed-side teaching

••PBL (problem based learning)

••Other…

5. What aspects of the EBM program work best? (Probe responses)

6. How can the teaching of EBM be improved? (Probe responses)

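### The student-type ANOVAs ignore the randomised tutorial groups, and each student type comes from one setting, so type-specific results will look too precise and cannot be attributed to entry type

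*Protocol article*

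**What the plan says.** The Recruitment section says that students are "randomly placed in small tutorial groups for their EBP teaching (approximately 20–25 in a group", and the Randomisation section makes the tutorial group the unit of allocation, by simple cluster randomisation with no stratification stated.

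The Sample size calculation sets "A minimum of 120 students per arm", made up of "40 from each of metropolitan Melbourne (undergraduate), rural Victoria (graduate) and Monash Malaysia (international". Each student type is thereby tied to one setting.

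For the comparison by type, the Analyses section says: "Differences between intervention/control groups and student type (undergraduate/graduate/international) will be explored using one and two-way" ANOVA, where appropriate. It mentions no cluster term and no cluster-level summary. The Discussion then says: "It will also provide evidence on the effectiveness of blended learning across medical student cohorts; be it undergraduate, graduate and international students".

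**The concern.** There are two separate difficulties.

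**Error unit.** Students taught in the same group share a tutor-led course and are allocated together. An ordinary one- or two-way ANOVA treats them as independent. With about two groups per arm-by-type cell, variation between groups is estimated from very few units, and the ANOVA replaces it with variation between students. Chance differences between groups can then appear as a student-type effect or as a type-specific benefit of blended learning.

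**Attribution.** The factor is called student type, but under the recruitment plan its levels coincide with metropolitan Melbourne, rural Victoria and Malaysia. If the effect of blended learning differs across the three levels, these data cannot show whether entry type or region is responsible.

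The Discussion offers evidence for undergraduate, graduate and international students as such. A school deciding which entry stream should receive blended teaching could be misled on both counts.

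**Working it through.** **The plan's own figure.** The target is 120 per arm, and the plan says that this number "will be recruited to detect a 50% difference in EBP competency". No reference mean is given, so 120 cannot be reproduced. With SD 2.8, two-sided α 0.05 (sidedness is not stated) and 0.80 read as power, 120 per arm corresponds to a difference of 2.80 × 2.8 × √(2/120) = 1.01 points. No design effect is stated.

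**Inputs.** From the protocol: SD 2.8, 40 students per arm and type, groups of 20–25. Assumed: ICC 0, 0.02 and 0.05 (wider where stated), two groups of 20 per cell, and an even split of groups between arms within each type.

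**Groups per cell.** 40/25 = 1.6 to 40/20 = 2.0. In total, 240/25 = 9.6 to 240/20 = 12 groups.

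**Error degrees of freedom, two-way layout (3 types × 2 arms = 6 cells).**
- Students as units: 240 − 6 = 234.
- Groups as units: 12 − 6 = 6, and fewer with groups of 25.

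**95% half-width for the arm effect within one type.**
- Student level: SE = 2.8 × √(2/40) = 0.626, and 1.99 × 0.626 = 1.25 points.
- Group level: SE = √(2 × 2.8² × (ICC + (1 − ICC)/20) / 2). The joint analysis pools the between-group variance over the six cells (6 df, t = 2.447). A stand-alone analysis of one type has 2 df (t = 4.303).

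| Assumed ICC | SE | Joint, 6 df | One type alone, 2 df |
|---|---|---|---|
| 0 | 0.626 | 1.53 | 2.69 |
| 0.02 | 0.735 | 1.80 | 3.16 |
| 0.05 | 0.874 | 2.14 | 3.76 |

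Against 1.25, the joint half-widths are 22%, 44% and 71% wider (1.53/1.25, 1.80/1.25, 2.14/1.25). At ICC 0 the SE is unchanged and the whole difference is the price of fewer degrees of freedom. Only at a positive ICC is the student-level SE itself too small.

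**False-positive rate.** In a simulation of 40,000 trials with this layout, a nominal 5% student-level interaction test rejected a true null in 8%, 22% and 37% of trials at assumed ICCs of 0.01, 0.05 and 0.10. The test of the student-type main effect gave the same rounded figures. At ICC 0 both were close to 5%.

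**Power for a difference in effect between two types.** Even with independent students, SE = 2.8 × √(4/40) = 0.885, and 2.80 × 0.885 = 2.48 points is detectable at 80% power, against 1.01 for the pooled comparison.

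**Balance.** Randomisation is unstratified, so two groups per arm in each type is an expectation. If 12 groups (four per type) are split 6:6, all three types split 2:2 with probability 23%. At least one type falls wholly in one arm with probability 14%, which leaves no comparison within that type.

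**Attribution.** The Sample size calculation gives a one-to-one map: undergraduate to metropolitan Melbourne, graduate to rural Victoria, international to Malaysia. A contrast between two types is therefore the same contrast as that between two regions, and no model fitted to these data can separate them.

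**The case against.** The strongest reply has four parts.

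*The clustering fault belongs to the primary t-test.* The t-test does share it. But the ANOVAs are separately named analyses, and correcting the t-test would change neither them nor the link between type and region.

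*The analysis is only exploratory.* This is fair. The protocol speaks of exploring and of providing evidence, the stated objectives do not mention student type, and no power is claimed for it. A reader might infer that firm cohort-specific conclusions are promised, but the text does not go that far. The low power for an interaction is the usual limit of a subgroup analysis. Exploratory intervals must still use the right error term.

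*The numbers can be overstated.* A reader might take half-widths of 2.7 to 3.8 points as the cost of clustering. Those apply only if one type is analysed alone on 2 df. A joint analysis gives about 1.5 to 2.1. Two groups per cell is also what the minimum recruitment yields. More could be enrolled, and students may decline, so 40 participants may need more than two groups.

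*The confounding can be overstated.* A reader might infer that type is confounded with each hospital and tutor. The Settings section lists seven metropolitan and six rural hospitals, so hospitals can vary within two of the types, and nothing is said about how tutors are assigned. A reader might also infer overlapping categories from "Monash University runs undergraduate and graduate-entry MBBS programs, in both Australia and Malaysia". That sentence describes programmes offered, whereas the recruitment plan places each analysed type in one setting. What stands is that type and region coincide.

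A planned two-way ANOVA can already hold the arm-by-type interaction. The structure is therefore usable, and what is wrong is the error term and the label.

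**Conclusion.** The point holds and should be corrected. As written, the student-type ANOVAs use students as the error unit in a trial that randomises tutorial groups, with about 234 error degrees of freedom in place of about 6 at the minimum recruitment. The within-type half-width should be about 1.5 to 2.1 points rather than 1.25 over assumed ICCs of 0 to 0.05. This rests on two groups of 20 per cell, an even split between arms, a between-group variance common to all cells, and a reading of the named tests as unadjusted because no adjustment is stated. With an ICC near zero the inflation of false positives is small. With more groups the loss of degrees of freedom shrinks.

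Separately, and whatever the ICC, a type difference or type-by-arm interaction cannot be told apart from a regional one. This limits attribution. It does not bias the randomised comparison within a setting.

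**What to change.** - Replace the one- and two-way ANOVAs with a single arm-by-campus-cohort interaction, in a model or cluster-level analysis that accounts for tutorial group and uses small-sample degrees of freedom.
- Label the factor campus cohort, with levels metropolitan Melbourne, rural Victoria and Malaysia.
- Report cohort-specific estimates with cluster-based intervals, marked as exploratory.
- Amend the Discussion sentence to say that differences between cohorts cannot be attributed to entry type.

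The cost is revised wording, wider intervals and a softer claim. No new data are needed, but tutorial-group membership must be available in the analysis data set.

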### Ethics

Ethical approval for this study has been obtained from the Monash University Human Research Ethics Committee.

### Qualitative research methodology

The following outlines the protocol for the qualitative case study of the research.

### Recruitment

At the conclusion of the RCT, students from the 13 Australian hospital sites who received the intervention will be invited to participate in focus groups using a convenience sampling approach [13]. Participants will be required to provide written consent prior to their participation in the qualitative case study.

### Data collection

A minimum of three focus groups composed of students based at metropolitan and rural hospital sites (including Australian and Malaysian study sites), will be performed by an independent facilitator. All focus group discussions will be guided by a semi-structured interview schedule (Appendix 1). Each focus group will be comprised of between six and eight students, and will be digitally recorded and transcribed verbatim at the conclusion of the focus groups. Focus groups will be performed until the data reaches a point of theoretical saturation (i.e. no new discussion points are raised, which haven’t already been raised in previous focus groups) [13].

### Data analysis

Transcripts from all focus groups will be analysed independently by two researchers using thematic analysis [13]. The thematic analysis will comprise of a six step approach including; (i) familiarization of the data achieved by reading each transcript, (ii) generation of preliminary codes, (iii) searching for themes from the preliminary codes, (iv) creation of thematic map, (v) specific definition and naming of themes and (vi) final analysis [14]. The two sets of thematic analysis will be compared before a final iteration of thematic analysis is performed and final themes generated and consensus is reached. Thematic analysis will be assisted with the use of the NVivo software program [15]. Data analysis of the quantitative and qualitative results will be performed utilising a concurrent triangulation design [16]. This approach permits immediate collation and analysis of data, promoting triangulation of the data, with the quantitative results determining the effectiveness of the intervention, whilst the qualitative data contextualising the results and probing the participants’ perceptions and attitudes toward the intervention [16].

## Discussion

It has been more than 20 years since the term 'evidence based practice’ first emerged, yet there is currently little evidence to guide educators on how to teach EBP to health professionals. This study will provide novel RCT evidence regarding the effectiveness of blended learning as a methodological approach for teaching EBP in medical schools. It will also provide evidence on the effectiveness of blended learning across medical student cohorts; be it undergraduate, graduate and international students. It will also provide valuable qualitative data to contextualise results, particularly student perception of competency in EBP.

## Appendix 1

Interview schedule used to guide focus group discussions

1. What type of material do you prefer to be taught in; (and why)

••Lecture format

••Tutorial format

••Small groups

••Self-directed

••Online

••Workshops

2. How is EBM best delivered (probe reasoning for responses)

••Lecture

••Tutorial

••Online

••Combination etc…

3. Would 'flip’ learning suit the teaching of EBM (i.e. pre-loading information before class)? (probe reasoning for responses)

4. Should EBM teaching be blended with;

••Bed-side teaching

••PBL (problem based learning)

••Other…

5. What aspects of the EBM program work best? (Probe responses)

6. How can the teaching of EBM be improved? (Probe responses)
